#### Economic evaluation

To show the effects on the cost to the health care system, we will conduct an economic analysis of the days spent unable to work for the nursing and care staff members who are primarily involved in the care of the PWSDs.

Missing data will be imputed by using the expectation maximum (EM) algorithm. The data analysis will be performed with the “IBM SPSS Statistics 24” software. All analyses will be conducted under the supervision of the cooperation partner IMBE.

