### Intervention

The MAKS-s intervention is a multicomponent non-pharmacological intervention designed specifically for people with severe dementia. It consists of four components that are combined in the same order every day in a manualised intervention module lasting approximately 1 h. The participants have to use social skills in order to interact in a group. Social cooperation is promoted in all components.

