#### Implementation of the MAKS-s intervention

The nursing homes in the intervention group will commit themselves to carrying out the MAKS-s intervention in accordance with the manual every Monday, Wednesday, and Friday for 6 months. All study participants will participate in the intervention every day. MAKS-s will be carried out by two trained MAKS-s therapists, who have received 2 days of training. All materials used in the intervention will be given to the nursing homes in the intervention group at baseline and will be given to the control groups after the 6-month intervention period. Staff members at the study headquarters will be available to answer questions by phone or e-mail on weekdays. The project will not exert any influence over the pharmacological treatment of the participants or their individual participation in other activities. However, all these influences will be documented for all study participants. Due to findings from previous randomised-controlled trials, serious adverse events are not expected. Therefore, no stopping guidelines are necessary [10, 11].

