##### Secondary target group

*Professional Care Team Burden (PCTB) Scale* [43]*.* The PCTB is a self-rating scale for assessing the subjective burden of the professional care staff in nursing homes and other caregiving facilities. The measure contains 10 items divided into 3 subscales (structural burden, objective burden, subjective burden). The items are rated on a five-point scale ranging from strongly disagree to strongly agree. The total score ranges from 0 to 40 points, with lower values indicating higher burden.

The convergent validity was demonstrated by computing the correlation with the Perceived Stress Scale (PSS), indicating moderate to high validity [43]. Cronbach’s alpha for the complete scale was .79.

*Days spent unable to work*. The number of days spent unable to work by the nursing and care staff who are most involved in the care of the participating PWSDs will be recorded by the head of the nursing home.

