#### Other measures

*Mini-Mental State Examination (MMSE)* [44]*.* The MMSE is the most popular screening test for dementia [45]. It evaluates five domains of cognitive abilities: orientation, registration, attention and calculation, recall, and language. The score ranges from 0 to 30 points, and 0 to 9 points indicates severe dementia.

*Sociodemographic data, personal and medical history, and comorbidity index.* The following data on each participant’s medical history will be collected by the nursing home staff at baseline: sociodemographic data (age, sex), level of care, medications, and diagnosis. Comorbidities are weighted using the updated and validated Charlson Comorbidity Index (CCI) [46]. It is used to calculate the effect of 12 medical diagnoses on the mortality rate. Higher scores indicate a higher 1-year mortality rate. The 1-year mortality increases from 12% (index = 0) to 85% (index ≥5). Validity and excellent reliability have been demonstrated in several studies [47, 48].

*Monitoring form.* During the 6-month intervention period, every change in the health situation of the PWSD will be documented: change in the level of care, change in medication, additional diagnosis, hospitalisation, absences, death, and retirement from the MAKS-s intervention (intervention group only).

*Evaluation of MAKS-s.* The implementation of the MAKS-s intervention will be documented by the MAKS-s therapists every week. The attendance of every participant of the study will be recorded, along with deviations from the manual in order to monitor the intensity and the quality of the MAKS-s intervention.

*Additional/other regular activities.* All other activities, such as individual care, basal stimulation, singing, gymnastics, arts and crafts and so on, will be documented by the care staff every week.

*Continuation of the MAKS-s intervention.* To get indications of sustainability of MAKS-s, 12 months after baseline, all nursing homes participating in the study will be interviewed about the implementation of the intervention. They will be asked about the frequency, duration, number of participants, and whether it is practical to incorporate into the everyday routine.

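### The economic evaluation names only staff sick days, which give the cost of staff absence and cannot support the stated conclusion about health-care-system cost

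*Protocol article*

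**What the plan says.** The Economic evaluation section gives purpose and method in one sentence: "To show the effects on the cost to the health care system, we will conduct an economic analysis of the days spent unable to work". The sentence goes on to limit this to the staff most closely engaged in looking after the participating residents. It names no other cost item. Under Measures (Secondary target group), the days off work are a count that "will be recorded by the head of the nursing home".

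Other sections describe resources that the economic sentence does not mention:

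- **Delivery.** Implementation of the MAKS-s intervention says: "MAKS-s will be carried out by two trained MAKS-s therapists, who have received 2 days of training". Sessions run "every Monday, Wednesday, and Friday for 6 months", and the Intervention section describes "a manualised intervention module lasting approximately 1 h". The same Implementation section says that the materials are supplied to the homes.
- **Residents.** The monitoring form under Other measures covers "change in the level of care, change in medication, additional diagnosis, hospitalisation, absences, death" over the 6-month intervention period.
- **Documentation.** Also under Other measures, MAKS-s implementation and attendance are documented weekly, as are residents' other regular activities.

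No costing perspective or unit price is given. The Discussion's section on strengths and limitations does not qualify the system-cost aim.

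**The concern.** The aim and the method in that sentence do not match. The aim is an effect on the cost to the health care system. The method values one consequence of the intervention, staff absence, and sets nothing against it. MAKS-s uses staff time, training and materials, and it may change residents' use of hospital care and medication. A comparison that leaves all of this out cannot say whether system cost rises, falls or stays the same.

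What is at stake is the label on the result. A reduction in sick days reported under the stated aim could be read as a system saving. The sponsor listed in Table 2 is the national association of the statutory health and long-term care insurance funds, so a figure labelled as system cost is likely to matter to its reader.

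**Working it through.** The article gives no cost, saving or unit price, so there is no stated figure to reproduce. The check is a count of the delivery time that the economic sentence leaves out, expressed in sick days per staff member.

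**Inputs from the article**

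- 2 therapists per session, 3 sessions a week for 6 months, 2 training days (Implementation of the MAKS-s intervention).
- About 1 h per session (Intervention). The parts in Table 3 agree: 10 + 20 + 10 + 20 = 60 min.
- At least 6 staff participants per home (Sample size estimation, Secondary target group).
- At least 24 homes (Recruitment strategies).

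**Assumptions the article does not fix**

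- 26 weeks and an 8-hour day.
- Exactly 6 staff per home.
- 12 intervention homes (an equal split).
- The training days apply to each therapist and are charged in full to the 6 months.
- A delivery day is priced like a lost day.
- Materials and preparation are not counted.

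**Time per intervention home over 6 months**

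- Sessions: 2 × 1 h × 3 × 26 = 156 h.
- Training: 2 × 2 × 8 h = 32 h.
- Total: 156 + 32 = 188 h, and 188 / 8 = 23.5 person-days.
- Across 12 homes: 12 × 188 = 2,256 h, or 282 person-days.

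**Break-even reduction in sick days per staff member**, by the share of session time that replaces activities the home would have run anyway:

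| Share displaced | Calculation | Days |
|---|---|---|
| None | (156 + 32) / 8 / 6 | 3.9 |
| Half | (78 + 32) / 8 / 6 | 2.3 |
| All | 32 / 8 / 6 | 0.7 |

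**Sensitivity with no displacement**

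- 24 weeks, 8-hour day: (144 / 8 + 4) / 6 = 3.7 days.
- 26 weeks, 7-hour day: (156 / 7 + 4) / 6 = 4.4 days.
- With 10 staff per home, the same two cases give 22.0 / 10 = 2.2 and 26.3 / 10 = 2.6 days.

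Reductions below the applicable break-even would appear as lower absence cost in the planned analysis, but would be outweighed by delivery and training time once that is counted. Reductions above it would still not establish a system-cost effect, because resident resource use is not in the sum.

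**The case against.** **This is a condensed article.** Perspective, cost inventory and unit prices commonly sit in a fuller plan, and a fuller plan may add components. That stands for the details, and their absence is not the point here. But the sentence itself pairs a system-cost aim with one named item, and nothing else in the article widens it.

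**The natural reading is narrower.** Hypothesis IV and the t-test under Data analysis both concern sick days, so the economic sentence probably means to put a money value on that outcome. This is plausible, and it is why a wording change is enough. As written, however, the aim goes further than that.

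**Delivery time may not be a system cost.** It may fall on the home, or be redeployed from existing activities; the abstract stresses that available employees carry out the intervention. This stands: the perspective is undefined. The same uncertainty applies to sick days, so it gives no reason to count one staff-time item and omit the other.

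**The break-even is soft.** This also stands. It runs from 0.7 to about 4.4 days on assumptions the article does not fix, and no expected sick-day effect is stated. It cannot be shown that the sign would reverse, only that it could.

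**Stronger readings.** A reader might infer that the trial will report a net saving and that the result is biased in favour of MAKS-s. The article promises no net saving and no cost-effectiveness result. Omitting delivery cost would favour MAKS-s, but omitting resident resource use could hide savings as easily as costs. A reader might also infer that a rise in hospital use would go unseen. It would not: hospitalisation is recorded on the monitoring form and is merely not named in the economic analysis.

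**Conclusion.** The point holds as a mismatch between stated aim and stated method. Sick days of the most involved staff measure the cost of staff absence and do not support a conclusion about health-care-system cost. With 6 staff per home, an 8-hour day, 26 weeks and equal pricing of delivery and lost days, the omitted delivery and training time is worth about 0.7 to 4 sick days per staff member over 6 months, depending on how much existing activity MAKS-s displaces. That is large enough for a modest reduction in absence to go with a net cost, but this remains a risk and not a result the article announces.

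Priority is minor. Sick days are a key secondary outcome in Table 2, but cost appears in none of the four hypotheses and among none of the listed outcomes. No efficacy conclusion depends on it.

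**What to change.** Either of two changes resolves it.

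1. **Narrow the claim.** Restate the aim and conclusion of the economic evaluation as the cost of staff absence, and make no claim about health-care-system cost. This costs nothing.
2. **Widen the analysis.** State the costing perspective. Set delivery cost against sick-day cost, using documented sessions, training and materials, net of displaced activities. Add recorded hospitalisations and medication changes as that perspective requires. Report the net difference between arms. Because the weekly records are described as covering implementation and attendance, not therapist hours, hours may have to be derived from sessions held.

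The second option needs unit prices and some extra analysis, mostly of data already documented. Its downside is a possibly less favourable economic figure.

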## Discussion

In this article, we described the design of a cluster-randomised controlled study on the effects of a multicomponent intervention for PWSD carried out in nursing homes. The effects of the intervention on the nursing home staff will also be investigated.

BPSD are the most challenging and the most burdensome side effects of this disease when it is in its severe stages. In addition to the formal caregivers, the PWSDs also suffer [17]. This indicates that the reduction of BPSD should be the main aim of a psychosocial intervention to reduce the strain of the formal caregivers and improve the quality of life of the PWSDs. The intervention described in this study is designed to reduce non-cognitive symptoms by providing a multicomponent intervention to meet the needs of the PWSDs.

### Strengths and limitations of the study design

The study design offers several strengths. The external validity of the study is high because of the naturalistic setting in nursing homes with nursing staff and the recruitment of nursing homes that are in different federal states of Germany, are in urban and rural regions, and are run by a wide variety of organisations (profit, non-profit, local authorities). Also the duration of the intervention of 6 months, the use of a manualised treatment, and the focus on two target groups (PWSDs and the nursing and care staff) have rarely been applied in international studies [15, 25, 49–51].

Another strength of the current study is the cluster randomisation. We decided to use cluster randomisation rather than randomisation because of the secondary target group. If we were to have a treatment group and a control group in the same nursing home, we could not observe any effect of the intervention on the formal caregivers because the caregivers may be responsible for both the people in the intervention group and the people in the control group. Furthermore, the intervention could not be withheld from any individual working in a nursing home without the possibility of “contaminating” the control group [52]. In order to avoid a systematic difference between the two arms of the study by chance, a three-step stratification process is being conducted to allocate the nursing homes. At the same time, to avoid a recruiting bias, recruitment will be completed before randomisation.

However, a limiting bias can occur. Because we are conducting a non-pharmacological intervention, the nurses who carry out the assessments (raters) are not completely blind to the conditions of the study because they know about the group assignment.

Because the study deals with PWSDs, due to the severe cognitive impairment of the participants, we could only use proxy-based ratings from an observer’s perspective. The perspective of the PWSDs themselves cannot be taken into account.

Because participating in the study requires extra work by the nursing home staff, the facilities of the control groups may be less motivated because they will not receive the intervention during the first 6 months. To motivate them, they will also receive the intervention at the end of the 6-month intervention period (waitlist control group). As the control group will also be trained in the MAKS-s intervention after a delay of 6 months, important indications for implementation can emerge.

## Data Availability

The research group intends to publish data generated from this study in open-access, peer-reviewed journals. The datasets used and/or analysed during the current study will be available from the corresponding author ([contact]) on reasonable request.

## Abbreviations

ADLs: Activities of daily living
BPSD: Behavioural and psychological symptoms of dementia
MMSE: Mini-Mental State Examination
NPI-NH: Neuropsychiatric inventory nursing home version
PCTB: Professional Care Team Burden Scale
PWSD: Person with severe dementia
Qol: Quality of life
